## Abstract

**Background:**

Pharmacological therapies of proven efficacy in coronavirus disease 2019 (COVID-19) are still lacking. We have identified IFNβ-1a as the most promising drug to be repurposed for COVID-19. The rationale relies on the evidence of IFNβ anti-viral activity in vitro against SARS-CoV-2 and animal models resembling SARS-CoV-2 infection and on a recent clinical trial where IFNβ was indicated as the key component of a successful therapeutic combination.

**Methods:**

This is a randomized, controlled, open-label, monocentric, phase II trial (INTERCOP trial). One hundred twenty-six patients with positive swab detection of SARS-CoV-2, radiological signs of pneumonia, and mild-to-moderate disease will be randomized 2:1 to IFNβ-1a in addition to standard of care vs standard of care alone. No other anti-viral drugs will be used as part of the regimens, both in the control and the intervention arms. IFNβ-1a will be administered subcutaneously at the dose of 44 mcg (equivalent to 12 million international units) three times per week, at least 48 h apart, for a total of 2 weeks. The primary outcome is the time to negative conversion of SARS-CoV-2 nasopharyngeal swabs. Secondary outcomes include improvement or worsening in a clinical severity score measured on a 7-point ordinal scale (including transfer to intensive care unit and death), oxygen- and ventilator-free days, mortality, changes in pulmonary computed tomography severity score, hospital stay duration, reduction of viral load measured on nasopharyngeal swabs, number of serious adverse events, and changes in biochemical markers of organ dysfunction. Exploratory outcomes include blood cell counts, cytokine and inflammatory profile, peripheral mRNA expression profiles of interferon-stimulated genes, and antibodies to SARS-CoV-2 and to IFNβ-1a. INTERCOP is the first study to specifically investigate the clinical benefits of IFNβ-1a in COVID-19 patients.

**Discussion:**

Potential implications of this trial are multifaceted: should the primary outcome be fulfilled and the treatment be safe, one may envisage that IFNβ-1a be used to reduce the infectivity of patients with mild-to moderate disease. In case IFNβ-1a reduced the duration of hospital stay and/or ameliorated the clinical status, it may become a cornerstone of COVID-19 treatment.

**Trial registration:**

EudraCT 2020-002458-25. Registered on May 11, 2020

ClinicalTrials.gov Identifier: NCT04449380

## Introduction

### Background and rationale {6a}

Type I interferons (interferon alpha and beta, IFNα and IFNβ) are cytokines with antiviral and immuno-modulatory effects. By virtue of these properties, IFNα was used in the past as a treatment for chronic Hepatitis-C [1], while IFNβ is one of the reference treatments in multiple sclerosis in two therapeutic formulations: IFNβ-1a and IFNβ-1b [2].

Previous investigation in severe acute respiratory syndrome coronavirus (SARS-CoV) [3] and Middle East respiratory syndrome coronavirus (MERS-CoV) [4] infections indicated that IFNβ might be a valid candidate to treat COVID-19.

While there are no clinical trials in SARS, a study testing IFNβ-1b in MERS patients is currently ongoing and results are expected by December 2020 (MIRACLE trial, NCT00419562).

In a mouse model of MERS, IFNβ-1b ameliorated the pulmonary function of infected mice when administered in therapeutic settings at a dose mirroring that currently used in the MIRACLE trial, although no changes in signs of acute lung injury were observed [5]. Moreover, IFNβ-1b was efficacious in the nonhuman primate common marmoset model of MERS [6].

A recent study of SARS-CoV-2 infection has reported that type III and type-I interferons are downregulated both in SARS-CoV-2 infected cells and in the lung tissue of patients deceased with COVID-19 [7], suggesting a pathogenic mechanism similar to that hypothesized for SARS-CoV and MERS-CoV [8]. Furthermore, some from our group have recently shown that IFNβ inhibits replication of SARS-CoV-2 in vitro [9]*.*

The unprecedented emergency of the COVID-19 pandemic, with no available drugs of proven efficacy, provided a compelling reason to repurpose drugs already marketed with other indications for treating SARS-CoV-2 infection. Among these, IFNβ looked immediately attractive and some clinical trials were started, including the World Health Organization (WHO) sponsored SOLIDARITY trial program, in which IFNβ is being tested in combination with lopinavir/ritonavir [10]. Furthermore, an open label, randomized trial showed that IFNβ-1b, in addition to lopinavir-ritonavir and ribavirin, was superior to lopinavir-ritonavir alone in shortening the time to negative conversion of nasal swabs for SARS-CoV-2, alleviating symptoms and reducing the duration of hospital stay [11]. The findings of this study indicate the urgent need of trials specifically addressed to test IFNβ efficacy in COVID-19 patients [12].

Timing of intervention might be crucial when it comes to COVID-19 immunomodulation. Since the clinical manifestations of SARS-COV-2 infection range from mild symptoms (fever, malaise, cough) to bilateral pneumonia leading to progressive respiratory failure, it is likely that a compound with both antiviral and immunomodulatory effects such as IFNβ would be most effective in the earliest stages of the disease. Nonetheless, IFNβ-1a is likely to be safe also in the case of progression to ARDS, as shown in a recent trial [13].

### Objectives {7}

The purpose of this randomized clinical trial is to test the efficacy and safety of IFNβ-1a in COVID-19 patients at early stages of SARS-COV-2 infection. Patients identified as suitable for the enrolment are those symptomatic at the time of diagnosis, with mild-to-moderate radiologic signs of pneumonia and no acute respiratory distress syndrome (ARDS).

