### Eligibility criteria {10}

Participants will be patients aged 18 years or greater, diagnosed with COVID-19 (positive swab RT-PCR detection of SARS-CoV-2 and pneumonia diagnosed with computed tomography (CT)), and with a clinical status of 3, 4, or 5 on a 7-point ordinal scale, consisting of the following: (1) not hospitalized, with resumption of normal activities; (2) not hospitalized, but unable to resume normal activities; (3) hospitalized, not requiring supplemental oxygen; (4) hospitalized, requiring supplemental oxygen; (5) hospitalized, requiring high-flow oxygen therapy, non-invasive mechanical ventilation, or both; (6) hospitalized, requiring extracorporeal membrane oxygenation (ECMO), invasive mechanical ventilation, or both; and (7) death. Exclusion criteria include clinical status defined as category 1, 2, or 6 on the aforementioned 7-point ordinal scale, known allergy or hypersensitivity to IFNβ-1a or IFNβ-1b; presence of severe concomitant illnesses and/or medical conditions that in the physician opinion will not allow participation to the study; pregnant or lactating females; history of major depression disorder or suicidal attempt or suicidal ideation; and spontaneous blood ALT or AST levels > 5 times the upper limit of normal. Starting from the signature of the informed consent, the patient will be considered enrolled in the clinical trial and subject to randomization. Interventions will be performed by the San Raffaele Hospital physicians assigned to the COVID-19 units.

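### The objective targets early-stage patients, but the eligibility criteria do not define early stage and no stated analysis accounts for time since symptom onset

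*Protocol article*

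**What the plan says.** The protocol article describes the target population in three places.

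- **Background and rationale {6a}:** "Timing of intervention might be crucial when it comes to COVID-19 immunomodulation". The next sentence considers it likely that a compound with antiviral and immunomodulatory action "such as IFNβ would be most effective in the earliest stages of the disease".
- **Objectives {7}:** the purpose is "to test the efficacy and safety of IFNβ-1a in COVID-19 patients at early stages of SARS-COV-2 infection". The following sentence describes suitable patients by three features: symptoms at diagnosis, mild-to-moderate pneumonia on imaging, and absence of ARDS.
- **Eligibility criteria {10}:** adults with a positive swab, pneumonia on CT, "and with a clinical status of 3, 4, or 5 on a 7-point ordinal scale". On severity, the exclusion reads "Exclusion criteria include clinical status defined as category 1, 2, or 6 on the aforementioned 7-point ordinal scale". Status 5, which is admitted, covers high-flow oxygen and non-invasive ventilation.

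On analysis, Statistical methods {20a} names a log-rank test and a Cox model for the primary outcome, with no covariates mentioned. Additional analyses {20b} states that no subgroup analyses are planned.

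**The concern.** The objective and the criteria describe different populations. The ordinal scale records current respiratory support. It does not measure time since infection, radiologic grade or ARDS. A patient late in the illness who is still swab-positive and on oxygen meets every listed criterion, and so does one without symptoms at diagnosis.

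This matters for the primary outcome, time to negative conversion of the swab. Time since onset plausibly affects how long clearance still takes and, on the protocol's own rationale, how much the drug can do. Two things are at stake. Patients treated late may dilute the effect the trial was sized to detect. And a null result would not distinguish an ineffective drug from late treatment, while a positive one would not show that early-stage patients were those who benefited.

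**Working it through.** **Text comparison**

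| Feature of the target group | Objectives {7} | Eligibility {10} |
|---|---|---|
| Stage | early | no definition, no limit on days from onset |
| Symptoms at diagnosis | yes | not listed |
| Radiologic grade | mild to moderate | pneumonia on CT, no grade |
| ARDS | absent | not listed; status 5 admitted, status 6 excluded |

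**Reproducing the plan's sample size**

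Inputs from Sample size {14}: medians 12 and 7 days, HR 0.58 (7/12 = 0.583), 80% power, 5% level (taken as two-sided), 2:1 allocation, 6 months of accrual, 29 days of follow-up.

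Schoenfeld: d = (1.960 + 0.842)² / [(2/3)(1/3)(ln 0.58)²] = 7.849 / (0.2222 × 0.2967) = 119.03, so 120 events. With uniform accrual over 180 days, a further 29 days and a common closing date, the event probability is 0.992. N = 120/0.992 = 121, in line with the stated 120. The point does not rest on a sample-size error.

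**Power before dilution**

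If each patient is followed for 29 days, the event probabilities are 1 − 2^(−29/12) = 0.813 (control) and 1 − 2^(−29/7) = 0.943 (interferon). Expected events are 40 × 0.813 + 80 × 0.943 = 108.0. Power = Φ(√(108.0 × 2/9) × |ln(7/12)| − 1.96) = Φ(0.68) = 75%. Simulated log-rank power is 73%. The gap to 80% comes from reading 29 days as each patient's follow-up. It is a separate matter, so the figures below should be read against 73-75%.

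**Dilution (illustration only)**

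Assume a share q of patients in both arms is late, the control median is 12 days throughout, and late patients keep a fraction f of the planned log hazard ratio. The average log HR is then (1 − q(1 − f)) × ln(7/12), and expected events are recalculated for the mix. Example with q = 20%, f = 0: 0.8 × 0.539 = 0.431, 105.9 events, power = Φ(√(105.9 × 2/9) × 0.431 − 1.96) = Φ(0.13) = 55%.

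| Late share q | HR, f = 0 | Power, f = 0: formula (simulated) | Power, f = 0.5: formula (simulated) |
|---|---|---|---|
| 0% | 0.583 | 75% (73%) | 75% (73%) |
| 10% | 0.616 | 66% (61%) | 71% (67%) |
| 20% | 0.650 | 55% (52%) | 66% (63%) |
| 30% | 0.686 | 45% (39%) | 61% (58%) |
| 50% | 0.764 | 25% (20%) | 50% (47%) |

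The simulations used 80 and 40 patients with 4,000 runs (f = 0) or 8,000 runs (f = 0.5). The formula runs somewhat above the simulation because it averages log hazards over a mixture.

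**The case against.** The best reply is that the protocol uses stage in a clinical sense, not in days. The Objectives section describes suitable patients by symptoms, imaging and ARDS, and the rationale places disease on a spectrum from mild symptoms to respiratory failure. The criteria do turn part of that into a rule: a positive swab is required and status 6 is excluded. This stands against any claim that the criteria ignore stage altogether. It does not remove the mismatch, because even the clinical descriptors in the objective are missing from the criteria.

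A reader might infer that the trial cannot test its own hypothesis. The documents do not support that. The hypothesis is superiority in time to negative conversion, and randomisation keeps that comparison valid for the enrolled mix. A reader might also infer that late patients will enter in large numbers or gain nothing. The rationale says only that timing might be crucial and that the effect is likely to be greatest early. No late share or late effect is given, and no benefit in late patients is the extreme case. Nor do the documents show that transfers from network hospitals lengthen the interval, since no transfer times are given.

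Finally, this is a condensed article, its schedule and flow-chart figures are not shown, and a separate analysis plan is promised. A window or covariate may exist there. That would turn the remedy into a correction of the article, but it would not make the objective and the criteria as printed agree.

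**Conclusion.** The point holds as a mismatch between objective and eligibility, with a probable cost in power and interpretation. It does not invalidate the comparison. Followed as written, the criteria can enrol patients whom the objective does not describe, and no stated analysis accounts for time since onset.

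The size cannot be fixed from the documents. If late patients had no benefit, power would be about 52% at 20% late and about 20% at 50% late (simulated), against 73-75% with none. If they kept half the log-hazard effect, it would be about 63% and 47%. All of this assumes exponential times, a 12-day control median for early and late patients alike, and 29 days of follow-up each. The equal control median is itself doubtful for patients already far into clearance.

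**What to change.** Reconcile Background {6a}, Objectives {7} and Eligibility {10} in one of two ways:

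1. Carry the objective's conditions (symptoms at diagnosis, radiologic grade, ARDS) and a definition of early stage chosen by the sponsor into the criteria, and state how status 5 fits with them; or
2. Remove the early-stage wording from the objective, so that it describes the patients the criteria admit.

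A day limit should not be borrowed from the trial that supplied the planning medians on the strength of this article, which does not report any onset window for that trial.

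In either case, record days from symptom onset to randomisation at baseline and include it as a prespecified covariate in the primary Cox model. Also report a supportive treatment-by-days-from-onset interaction. The main effect alone adjusts for timing but does not separate early from late response. With about 120 patients the interaction will be imprecise and should be presented as an estimate with its interval, not as a test that decides the trial.

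The cost is one CRF item, one or two model terms and an amendment to the text. Restricting entry would also shrink the pool somewhat. Recruitment {15} cites more than 1,000 admissions at the trial hospital and another 4,000 in the network from late February to the end of May 2020, against 126 needed. But it makes future access depend on a second outbreak, so a restriction is a real recruitment trade-off for the sponsor to weigh.

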### Trial design {8}

This is a superiority, randomized, controlled, open label, phase 2 clinical trial of IFNβ-1a in COVID-19 patients (INTERCOP). Recruited patients will be randomized 2:1 to either of two parallel arms: the intervention or the control arm.

## Methods: participants, interventions, and outcomes

### Study setting {9}

This clinical trial will enroll patients at the IRCCS San Raffaele Hospital, an academic hospital part of the Gruppo San Donato (GSD) hospital network located in Northern Italy. Patients admitted to other hospitals of GSD will be offered to participate to the trial: if they are admitted to the trial, they will be transferred to IRCCS San Raffaele.

### Eligibility criteria {10}

Participants will be patients aged 18 years or greater, diagnosed with COVID-19 (positive swab RT-PCR detection of SARS-CoV-2 and pneumonia diagnosed with computed tomography (CT)), and with a clinical status of 3, 4, or 5 on a 7-point ordinal scale, consisting of the following: (1) not hospitalized, with resumption of normal activities; (2) not hospitalized, but unable to resume normal activities; (3) hospitalized, not requiring supplemental oxygen; (4) hospitalized, requiring supplemental oxygen; (5) hospitalized, requiring high-flow oxygen therapy, non-invasive mechanical ventilation, or both; (6) hospitalized, requiring extracorporeal membrane oxygenation (ECMO), invasive mechanical ventilation, or both; and (7) death. Exclusion criteria include clinical status defined as category 1, 2, or 6 on the aforementioned 7-point ordinal scale, known allergy or hypersensitivity to IFNβ-1a or IFNβ-1b; presence of severe concomitant illnesses and/or medical conditions that in the physician opinion will not allow participation to the study; pregnant or lactating females; history of major depression disorder or suicidal attempt or suicidal ideation; and spontaneous blood ALT or AST levels > 5 times the upper limit of normal. Starting from the signature of the informed consent, the patient will be considered enrolled in the clinical trial and subject to randomization. Interventions will be performed by the San Raffaele Hospital physicians assigned to the COVID-19 units.

### Who will take informed consent? {26a}

Every patient will be informed about the modalities of the clinical study in accordance with the patient informed consent document, both in writing and verbally by the investigating physician. The informing physician and the patient must each personally sign and date the informed consent form with a declaration on data privacy. Every informed consent will be part of the investigator’s file and retained with it. The patient will retain a copy of the patient informed consent.

### Additional consent provisions for collection and use of participant data and biological specimens {26b}

In addition to consent to the trial, patients will be asked to sign a second informed consent for collection samples for mechanistic studies and the COVID-19 biobank project (COVID-BioB- ClinicalTrials.gov NCT04318366).

### Interventions

#### Explanation for the choice of comparators {6b}

Patients randomized to the intervention arm will receive IFNβ-1a in addition to standard of care, while patients of the control arm will receive standard of care only. The standard of care for COVID-19 patients at San Raffaele Hospital includes any pharmacological (e.g., antibiotics) and non-pharmacological (e.g., oxygen, ventilation) treatments prescribed on clinical grounds. In consideration of the emerging role of thrombosis in COVID-19 pathogenesis [14, 15] and in the absence of apparent indications of harm [16], heparin will be part of background therapy in all patients. In the absence of clear efficacy data in patients with mild-to-moderate disease [17, 18], no additional antiviral treatments (e.g., remdesivir, hydroxychloroquine, lopinavir/ritonavir) will be administered in either the experimental or the control arms. In case of ongoing therapies with hydroxychloroquine and/or lopinavir/ritonavir (e.g., as a general practitioner’s prescription), these drugs are discontinued prior to admission to the trial.

#### Intervention description {11a}

##### Intervention arm

IFNβ-1a Rebif® (Merck Europe BV, Amsterdam, The Netherlands) will be used as the investigational drug. IFNβ-1a will be administered subcutaneously at a dose of 44 mcg (equivalent to 12 million international units), three times per week at least 48 h apart, for a total of 2 weeks. All patients will receive a total dose of 264 mcg (72 million international units) under physician control; no dose adjustments are planned. This dose corresponds to that recommended in relapsing-remitting multiple sclerosis [19, 20]. There will not be gradual dose escalation in order to maximize drug effect in the quickest time.

##### Control arm

Any pharmacological (e.g., antibiotics) and non-pharmacological (e.g., oxygen, ventilation) treatments prescribed on clinical grounds.

#### Criteria for discontinuing or modifying allocated interventions {11b}

Patients may drop out of the clinical study at any time without stating reasons. This will not have any negative consequences for the patient’s further treatment.

Possible reasons for withdrawal are:
Withdrawal of consent.Any clinical condition that in the investigator’s opinion could become dangerous for the patient and prevent the good conduction of the clinical trial.Protocol violation that could compromise the quality of study data.Lack of co-operation/compliance of the patient.Occurrence of new diseases that could influence the treatment efficacy, for which the study medication is contraindicated or that are treated with a medication that is not permitted as a concomitant medication.Lack of experimental treatment administration due to failure to release the Medicinal Product lot.Lost to the follow-up.

The patients may withdraw from the study, if they decide to do so, at any time and for any reason.

Patients who have been withdrawn from the study cannot be re-included in the trial.

#### Strategies to improve adherence to interventions {11c}

Since the study drug is provided by the Hospital Pharmacy and has to be administered subcutaneously, the study nurse and medical staff involved in the trial will have direct control on drug administration.

#### Relevant concomitant care permitted or prohibited during the trial {11d}

Hydroxychloroquine, lopinavir/ritonavir, and remdesivir will not be administered as part of the standard therapeutic regimen, either in the intervention or in the control arms. Given the promising results of remdesivir in patients with severe disease [17], clinicians will be offered to administer remdesivir to patients with a clinical status of 6 on the 7-point ordinal scale.

### Provisions for post-trial care {30}

All patients hospitalized at San Raffaele with a diagnosis of COVID-19 are entering a post-discharge monitoring clinical program, independently on their participation to clinical trials. The purpose of this program is to identify physical and psychological dysfunctions left behind clinical recovery from SARS-CoV-2 infection. Participants to INTERCOP will be regularly followed-up in this program, having as an additional investigation a chest CT scan at 90 days, as per protocol.

### Outcomes {12}

#### Primary outcome

Time to negative conversion of SARS-CoV-2 nasopharyngeal swabs. Viral load will be measured by RT-PCR. [Time frame: baseline, days 3, 5, 7, 9, 11, 13, 15, 21, and 29]. IFNβ-1a has direct in vitro antiviral activity against SARS-CoV-2 [9], while IFNβ-1b has been identified as the key therapeutic reducing the time to negative conversion of SARS-CoV-2 nasopharyngeal swabs in a recent trial [11].

#### Secondary outcomes

I)Improvement in clinical severity score, defined as percentage of patients reporting each severity rating on a 7-point ordinal scale (as defined above in the “Eligibility criteria {10}” section). [Time frame: baseline, days 7, 15, 21, and 29]. This study is underpowered to measure clinical efficacy. Nevertheless, measuring changes in the distribution of patients on the 7-point ordinal scale allows both to monitor the safety of the therapeutic regimen and detect potential positive changes in the clinical status of patients.Improvement in clinical severity score, defined as the time to clinical improvement of two points from the time of randomization on a 7-category ordinal scale or live discharge from the hospital, whichever comes first (as defined above in the “Eligibility criteria {10}” section). [Time frame: from baseline to day 29].Incidence of new oxygen use, non-invasive ventilation, or high flow oxygen devices during the trial. [Time frame: from baseline to day 29].Oxygenation free days in the first 28 days. [Time Frame: from baseline to day 29].Ventilator free days in the first 28 days. [Time frame: from baseline to day 29].Incidence of new mechanical ventilation use during the trial. [Time frame: from baseline to day 29].Number of patients transferred to Intensive Care Unit (ICU). [Time frame: from baseline to day 29].II) Mortality rate. [Time frame: from baseline to day 29].III) Changes from baseline in pulmonary CT imaging severity score measured with artificial intelligence and expressed as cc and percent values of diseased lung (lung consolidation, ground glass opacities and disease free) [Time frame: baseline, day 21; extra follow-up at 90 days].IV) Duration of hospital stay expressed in days. [Time frame: from baseline to day 29].V) Viral load measured on plasma with RT-PCR. [Time frame: baseline, days 3, 5, 7, 9, 11, 13, 15, 21, and 29].VI)Number of serious adverse events (SAE) and adverse drug reaction (expected and un-expected) until the discharge from the clinical unit (discharge for any motivation). [Time frame: from baseline to day 29]. This outcome addresses safety.Changes from baseline in white blood cell count (WBC), hemoglobin, platelets, C-reactive protein (CRP), lactate dehydrogenase (LDH), alanine aminotransferase (ALT), aspartate aminotransferase (AST), total bilirubin, creatinine, prothrombin time, international normalized ratio (INR), D-dimer, electrolytes (sodium, potassium, calcium), and glucose. [Time frame: baseline, days 7, 15, and 29]. IFNβ exerts broad-range effects on the immune system, being anemia, thrombocytopenia, and leukopenia reported as common events [21]. Thus, monitoring these markers, in conjunction with markers of inflammation, coagulation, and organ dysfunction, is of pivotal relevance to address safety.

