### Statistical methods

#### Statistical methods for primary and secondary outcomes {20a}

Prior to the analysis of the final study data, a detailed statistical analysis plan (SAP) will be written describing all analyses that will be performed. Continuous variables will be described by mean, standard deviation, median, minimum, and maximum. Categorical variables will be described by number and percentage of subjects in each category. The primary efficacy analysis will be done on an intent to treat basis (ITT) and will include all randomized patients. Survival analysis will be performed to address the primary outcome of the study. Time to event is defined as the time from randomization until date of negative conversion. The date of the event (time of negative conversion) is the date of the first negative nasal swab test, confirmed by a second test performed at least 48 h apart. Data for dead patients are censored at the time of the last nasal swab. Survival curves will be estimated using the Kaplan-Meier method and the Log-rank test will be used to compare the outcomes of the different treatment arms. Hazard ratios will be estimated using the Cox proportional hazards model and these will be presented together with 95% two-sided confidence intervals. Endpoints that are measured as time from randomization will be compared between treatment groups using the Log-rank test. Student’s *t* test or Mann-Whitney test (depending on the data distribution pattern) will be used for inter-group comparison of continuous variables; chi-square test or Fisher exact test will be used for inter-group comparison of categorical variables. The primary analysis set for safety analyses is defined as the safety analysis set, which will include all participants who are randomized and have received at least 1 dose of study treatment. All safety data collected from the randomization date through the last follow-up visit will be summarized by treatment group. Statistical significance will be determined at 5% significance level. Analysis will be performed by SAS software Version 9.2 or later (SAS Institute, Inc., Cary, North Carolina, USA).

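### The new-oxygen/NIV/high-flow outcome overlaps the entry statuses and, like new mechanical ventilation, omits worse events; analyse worsening from each patient's own baseline instead

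*Protocol article*

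**What the plan says.** All references are to the protocol article. Under Eligibility criteria {10}, patients enter "with a clinical status of 3, 4, or 5 on a 7-point ordinal scale". Status 3 means hospitalized without oxygen. The next two categories are "4) hospitalized, requiring supplemental oxygen" and "5) hospitalized, requiring high-flow oxygen therapy, non-invasive mechanical ventilation, or both". Invasive ventilation or ECMO is status 6 and death is status 7. Status 6 is barred at entry: "Exclusion criteria include clinical status defined as category 1, 2, or 6 on the aforementioned 7-point ordinal scale".

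Under Secondary outcomes, item I lists two incidence measures, both to day 29:
- the escalation outcome: "Incidence of new oxygen use, non-invasive ventilation, or high flow oxygen devices during the trial";
- the ventilation outcome: "Incidence of new mechanical ventilation use during the trial".

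Neither entry says how newness is judged against entry status or how death counts. The ventilation outcome does not say whether NIV is included.

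Statistical methods {20a} gives the test for such outcomes: "chi-square test or Fisher exact test will be used for inter-group comparison of categorical variables". It mentions no adjustment for entry status. Sequence generation {16a} describes permuted blocks and mentions no stratification by status.

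The same list of secondary outcomes also has the distribution over the 7-point scale, ventilator-free days, ICU transfers and, as item II, "Mortality rate. [Time frame: from baseline to day 29".

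**The concern.** The escalation outcome does not mean the same thing for every patient. What can count as an event depends on where the patient started, and those who start highest have almost nothing left to count. It is also not ordered by severity. A patient who needs low-flow oxygen for a day and recovers has an event, while one who goes straight to intubation, or who dies without a new device, has none. The ventilation outcome has the second problem for deaths without ventilation.

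At stake is the reading of these two measures on their own. A lower incidence in one arm could reflect less deterioration, more patients already on support at entry, or more patients who bypassed the listed steps. The unadjusted test does not separate these.

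**Working it through.** The plan states no rate, power or entry mix for these two outcomes, so there is no figure of its own to reproduce. The only inputs from the plan are the arm sizes under Sample size {14}: 84 on IFNβ-1a and 42 on standard of care. All other inputs below are assumptions.

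**Step 1. Which events are open to whom (escalation outcome)**

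| Entry status | Already receiving | Components still possible |
|---|---|---|
| 3 | nothing | oxygen, high-flow, NIV |
| 4 | oxygen | high-flow, NIV |
| 5 | high-flow and/or NIV | at most a switch between the two; none if on both |

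**Step 2. How the worse courses score as worded**

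| Course | Escalation outcome | Ventilation outcome | Captured elsewhere |
|---|---|---|---|
| Status 3 or 4, intubated directly | no event | event | 7-point distribution |
| Status 5, intubated | no event | event if invasive only; unclear if NIV is included and the patient entered on NIV | 7-point distribution |
| Any status, dies without new support | no event | no event | mortality, 7-point distribution |

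**Step 3. Does the ventilation outcome overlap entry status?** If it means invasive ventilation, no: status 6 is excluded at entry. If it includes NIV, yes: some status-5 patients already have it, and a new NIV start would count in both outcomes. The eligibility scale uses the term mechanical ventilation for both kinds, each with a qualifier. The outcome has no qualifier.

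**Step 4. Dilution, if all randomized patients form the denominator.** Assume a 30% risk at statuses 3 and 4, none counted at status 5, and a status-5 share p. The displayed incidence is 0.30 × (1 − p).
- p = 10%: 0.30 × 0.90 = 27%. Status-5 patients: 42 × 0.10 ≈ 4 control, 84 × 0.10 ≈ 8 IFNβ-1a.
- p = 30%: 0.30 × 0.70 = 21%. Status-5 patients: 42 × 0.30 ≈ 13 control, 84 × 0.30 ≈ 25 IFNβ-1a.

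**Step 5. Chance imbalance in the status-5 share.** The SD of the between-arm difference in the share is √[p(1 − p)(1/84 + 1/42)]. At p = 15% this is √(0.1275 × 0.0357) = 0.067, or 6.7 points. That is imbalance in a baseline share. Its effect on the outcome is the imbalance times the risk gap between strata: 6.7 × 0.30 ≈ 2 points. At p = 10% the same steps give 5.7 × 0.30 ≈ 1.7 points, and at p = 30% they give 8.7 × 0.30 ≈ 2.6 points.

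**Step 6. Weight of one patient.** In the control arm, one course scored as no event moves the rate by 1/42 = 2.4 points.

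**Step 7. Direction (constructed example).** Let ventilation or death occur in 20% of each arm, with death without ventilation in 5% of controls and 10% of IFNβ-1a patients. The ventilation incidence is then 20 − 5 = 15% against 20 − 10 = 10%. The arm with more unventilated deaths looks better on this measure alone. The documents give no frequency for such deaths.

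**The case against.** The strongest reply is that this reads silence as a rule. Incidence of new use is naturally taken among patients not already on that support. The all-randomized denominator in Step 4 is not stated: the intention-to-treat sentence in Statistical methods {20a} concerns the primary efficacy analysis. At-risk sets for secondary outcomes commonly sit in the SAP, which the article promises and which is not shown. This stands, and the missing denominator alone would be no finding. It does not remove the rest, because the component list, which omits status 6 and death, and the unadjusted test are both stated.

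Several stronger readings are tempting and are not supported:
- *Both outcomes overlap entry status.* For the ventilation outcome this holds only if NIV is included. Because the escalation outcome names NIV separately, invasive-only is a natural reading.
- *Status-5 patients can never have an event.* A patient on high-flow alone can newly need NIV, and the reverse.
- *The trial ignores its worst events.* Direct intubation missed by the escalation outcome counts in the ventilation outcome, and deaths count under mortality and as status 7.
- *A measure that the protocol uses to monitor safety points the wrong way.* The safety-monitoring remark under Secondary outcomes concerns the 7-point distribution, which includes statuses 6 and 7. Neither of these outcomes is given that role.
- *Imbalance of about 7 points biases the result.* That figure is an SD of an assumed baseline share. Randomization leaves the comparison unbiased in expectation, and the effect on the outcome is nearer 2 points under the assumptions above.

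**Conclusion.** The concern holds as a minor-to-moderate weakness of two secondary measures. From the wording alone, the escalation outcome counts as events the supports that define entry statuses 4 and 5, and gives no event to direct intubation or to death without new support. The ventilation outcome gives no event to death without ventilation and leaves its own scope open. The stated comparison is unadjusted for entry status.

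The size cannot be fixed from the documents. It depends on the entry mix, on how often patients bypass the listed steps, and on a denominator that the SAP may define. Under the assumptions shown, dilution is 3 to 9 points from a 30% risk, and chance imbalance in entry status contributes roughly 2 points. This is not a demonstrated scoring error. The primary outcome and the sample size of 126 are untouched.

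**What to change.** 1. Analyse worsening by day 29 to any category above the patient's own baseline category, counting status 6 and death as events. Since nobody enters at status 6 or 7, every patient can then have an event.
2. Compare the arms stratified by baseline status (3, 4, 5), for example with a Cochran-Mantel-Haenszel test, or with a model adjusted for it, in place of the unadjusted chi-square or Fisher test.
3. Report component incidences only among patients not already on that support: new oxygen in status 3, new high-flow or NIV in statuses 3 and 4 (with a stated rule for switches within status 5), and new invasive ventilation in all. State whether death counts as an event or as a competing event.
4. State whether mechanical ventilation means invasive only.

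Entry status, support use and deaths are already needed for the listed outcomes, so no new data are collected. The costs are smaller denominators for the components, some repetition of what the 7-point distribution shows, and a documented change to secondary outcome wording. Recruitment began in July 2020 (Trial status), so the change should be dated and made without reference to results by arm, and go through the amendment route under {25} if judged to affect study conduct.
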